
# OBJECTIVES/AIMS

The goal of this research is to advance the science of multilevel mental health interventions that aim to reduce the disparate, adverse mental health, behavioral, and socioeconomic consequences of the COVID-19 pandemic that are a result of complex interactions between underlying structural inequities and numerous barriers to health care. This community-based participatory research study builds on a long-standing collaboration with 5 community-based organizations (CBOs) and employs a longitudinal waitlist control group design with 5 time points over 32 months. A random probability sample of 1000 Latinx immigrants (RS) will be compared with 240 Latinx immigrants and 60 African refugees recruited through CBOs and randomly assigned to an efficacious peer advocacy and learning model (RIWP; n=150) or a treatment-as-usual waitlist control group (TAU; n=150). This innovative design allows for testing of three nested levels of intervention: 1) peer intervention model; 2) engagement with CBOs; and 3) structural interventions expected in response to the pandemic (e.g., state relief for mixed status families and expanded health insurance coverage), to which all 1300 participants would potentially be exposed. We propose three primary aims to advance mental health intervention and disparities research:

**Aim 1.** Test the effects of the RIWP intervention to reduce adverse consequences of the COVID-19 pandemic for Latinx and Black immigrants and refugees.

**1.1** *Primary Outcomes:* RIWP participants will have decreased psychological distress, daily stressors, and economic precarity as compared to randomly assigned treatment-as-usual waitlist control group (TAU).

**1.2** *Secondary Outcomes:* RIWP participants will have increased protective factors (social support, access to resources, English proficiency, cultural connectedness, health services use).

**Aim 2.** Test the effects of engagement with CBOs to reduce adverse consequences of the COVID-19 pandemic for Latinx and Black immigrants and refugees.

**2.1** *Primary Outcomes:* CBO participants will have decreased psychological distress, daily stressors, and economic precarity as compared to the comparison group of randomly sampled immigrants (RS).

**2.2** *Secondary Outcomes:* CBO participants will have increased protective factors (social support, access to resources, English proficiency, cultural connectedness, health services use).

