Random assignment. Randomization of the CBO-recruited sample (n=300) into RIWP or treatment-as-usual waitlist control group (TAU) will occur after completion of timepoint 1 surveys and will be based upon a computerized algorithm that stratifies randomization by CBO site.

RIWP implementation. RIWP will be implemented with 30 participants from each CBO site (n=150) from Months 5-12. RIWP will be integrated into existing activities and services in different ways at each site, with the goal of creating a sustainable intervention and multilevel change. All RWIP activities (Learning Circles and advocacy) will be conducted remotely for now. Once state and UNM COVID restrictions are lifted, some in-person Learning Circles and advocacy meetings may occur. The treatment-as-usual waitlist control group will participate in RIWP after two years (3 timepoints) of data collection, from Months 29-35. RIWP involves a sustainable and replicable partnership model between refugees, CBOs, and universities (see Figure 1 for conceptual model). Newcomer families and undergraduate advocates work together for 16 weeks to: a) increase newcomers’ abilities to navigate their new communities; b) improve newcomers' access to community resources; c) enhance meaningful social roles by valuing newcomers' cultures, experiences, and knowledge; d) reduce newcomers' social isolation; and e) increase community responsiveness to newcomers. RIWP is implemented by university students enrolled in a 2-semester course, and has two elements: 1) Learning Circles, which involve cultural exchange and one-on-one learning opportunities; and 2) Advocacy, which involve collaborative efforts to mobilize community resources related to health, housing, employment, education, and legal issues and to create policy/system changes. Meeting in weekly Learning Circles, newcomers and their student partners learn from each other during cultural exchange time designed to facilitate sharing of cultural and intergenerational knowledge and to help newcomers recognize their contributions and potential to effect changes in their communities. During one-on-one learning time, newcomer and student participants practice English, fill out job applications, and engage in other activities newcomers want to pursue to expand knowledge, improve skills, or accomplish goals. RIWP is holistic, multilevel, and strengths-based, and has an explicit social justice orientation that is informed by an ecological perspective. A holistic intervention is essential because it addresses the multiple sources of newcomers’ psychological distress, including psychological (past traumas), material (poverty, lack of access to resources), physical (physical ailments from war, violence and deprivation), social (loss of meaningful social roles and social support), educational (limited English proficiency, literacy), and cultural disconnection from traditional cultural practices). A strengths-based perspective is important because newcomers have survived in the face of tremendous hardships and have numerous strengths on which to build, including cultural knowledge (and often extensive cross-cultural experience), resourcefulness (experience operating in resource scarce situations), effective coping strategies (that have enabled them to survive), multilingual abilities (many arrive already speaking two or more languages), and often strong family and community bonds and support. Newcomers are often pathologized by well-intentioned service providers and systems, rather than recognizing that most are resilient people who have faced abnormally difficult circumstances. Not only is it crucial for newcomers’ mental health and well-being to acknowledge their expertise and build upon their strengths, but also their knowledge and experiences are assets from which other Americans can benefit. Thus, mutual learning is an intentional and core component of RIWP. This emphasis also ensures that RIWP is appropriate for multiple linguistic and cultural groups who can participate simultaneously and learn from one another as well as from longer-term residents of the U.S. Guided by ecological theory, RIWP focuses not only on newcomers adjusting to their new contexts, but also on changing environments when they are inequitable or constraining (e.g., mobilization or redistribution of resources). Ensuring that RIWP creates change at multiple levels is important because newcomers have urgent learning, resource, and health needs that must be addressed at the individual level in order to enable them to work collectively with others to create community and structural changes that address the root causes of mental health disparities and social inequities, which result in sustainable social change.

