## *Data Analysis/**Statistical Considerations*

Quantitative data analysis. This longitudinal study design will use random effects (multilevel) models, which account for both repeated measures of individuals and the fact that in one arm individuals are clustered within CBOs. These models allow for outcomes to be missing under the MAR assumption (data is missing at random conditional on the observed outcomes and covariates),^89–91^ which we expect will be adequate. If there is a substantial amount of missing data for covariates or evidence that a more inclusive imputation model should be used, then we will use multilevel multiple imputation implemented via MITML package.^92^ Model assumptions will be evaluated using the comparison group for each analysis, and any modification to the analyses to address violations will be made before final analyses using only comparison group data.

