**Aim 1.** Test the effects of the RIWP intervention to reduce adverse consequences of the COVID-19 pandemic. The principal objective of this study is to test the efficacy of the RIWP intervention for participants recruited from CBOs. Because only individuals recruited from the CBO sample are eligible to be randomized to receive the RIWP intervention or treatment as usual, analysis for this aim includes only CBO participants. To examine the effects of the RIWP intervention, we propose a linear model with random effects for individuals. As randomization happens within CBO, there is not an explicit random effect for this included, but we do propose to use sandwich estimators,^99,100^ to adjust standard errors for any unexpected impacts of this clustering. In mixed notation the model for psychological distress is:

${Distress}_{ti}= B_{00}+{B_{01}\left( RIWP \right){+B}_{02}\left( Time \right){+B}_{03}\left( Time*RIWP \right){+\boldsymbol{B}}_{\mathbf{0}\boldsymbol{N}}\left( \boldsymbol{covariates} \right)+ r_{0ij}+r_{2ij}(Time)+ e}_{ij}$

where participation in the RIWP plus CBO is indicated by a dummy code for RIWP. Because baseline data is collected before randomization, time is centered at baseline and our aim is answered by B_03_ which is the difference in slopes of levels of distress, adjusted for covariates, between those who experience RWIP+CBO intervention and those in the CBO group.

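### The Aim 1 model names no term for CBO site, the stratification factor, and gives the stratification as its reason; adding site is a small but nearly free improvement

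*Protocol*

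**What the plan says.** Protocol, Data Collection Procedures (random assignment): allocation of the CBO-recruited sample "will be based upon a computerized algorithm that stratifies randomization by CBO site". Five sites contribute 60 people each, and 30 per site go to RIWP, so the design is 30:30 within each site.

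Protocol, Data Analysis/Statistical Considerations, Aim 1: the model contains RIWP, Time, Time*RIWP, an undefined covariate vector, and a random intercept and slope for each person. The test is B_03, the difference in slopes. On site, the text says "As randomization happens within CBO, there is not an explicit random effect for this included", and the same sentence goes on to propose sandwich estimators "to adjust standard errors for any unexpected impacts of this clustering".

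The opening paragraph of that section says that the models account for "the fact that in one arm individuals are clustered within CBOs". It lets outcomes be missing on the assumption that "data is missing at random conditional on the observed outcomes and covariates", with multilevel multiple imputation as a conditional fallback.

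The Aim 2 equation gives the same CBO participants a CBO random intercept (u_00j) and a CBO random slope (u_10j). The power paragraph uses a CBO ICC of .03 for Aims 2 and 3.

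**The concern.** When randomization is stratified, the arms are balanced within each stratum. A model-based analysis credits that balance only if the stratum is in the mean model. Otherwise, between-site differences stay in the person-level variance. The protocol treats within-site randomization as grounds for leaving site out, which reverses this logic.

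The protocol itself expects sites to differ. Aim 2 models site differences in level and trend, and one of the five sites consists entirely of African refugees while the other four recruit Latinx immigrants. B_03 is the principal test, so two things are at stake:

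- a standard error that does not match the design;
- missing-data handling that conditions on covariates among which site is not named.

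**Working it through.** **Inputs from the protocol (power paragraph):** d = .30, baseline-posttest correlation .68, 10% attrition (150 × .9 = 135 per arm), CBO ICC .03, stated Aim 1 power .91. Alpha is not given in that paragraph; I assume .05 two-sided.

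**1. Reproduce the stated power.** Residual variance after baseline adjustment: 1 − .68² = .5376. SE = √(2 × .5376/135) = .0892. Power = Φ(.30/.0892 − 1.96) = .919. This agrees with .91.

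**2. Standard error with site left out, pre/post approximation.** Leave the whole site variance τ² in the residual. The true sampling SD stays .0892, because the arms are balanced within sites.

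| τ² | Model-based SE | Overstatement | Power | Type I error |
| --- | --- | --- | --- | --- |
| 0 | .0892 | – | .919 | 5.0% |
| .03 (protocol ICC) | √(2 × .5676/135) = .0917 | 2.8% | .911 | 4.4% |
| .10 (assumed) | √(2 × .6376/135) = .0972 | 9% | .890 | 3.3% |

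If 3% is instead taken out of the existing residual when site is modelled, power rises from .919 to .927. If an ICC of .03 on total variance lies wholly in the residual, it rises to .933. Either way the difference at the protocol's ICC is about one point.

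**3. The planned estimand, a slope difference.** I simulated the Aim 1 random intercept and slope model with 5 sites × 60 people and 5 visits 8 months apart. The variances are assumptions: person intercept .68, person slope .02, residual .32, site intercept .03, site slope .003.

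- Site differences in level only: the model SE of B_03 is .0350 with or without site terms. Level differences do not touch the slope contrast in balanced data.
- Site differences in level and slope: .0356 without site terms and .0350 with them, an excess of about 2%. The empirical SD of the estimate is .0345 in both, so the estimator itself loses nothing. Test size is .042 without and .047 with; a second run gave .050 without, so any conservatism is slight.

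**4. Bias from dropout.** Same simulation, no true effect; dropout is the chance of loss at each of the four intervals.

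| Dropout pattern | Mean B_03 without site | Mean B_03 with site |
| --- | --- | --- |
| Depends on site, equal in both arms | −.0003 | −.0003 |
| RIWP .15 at sites with rising trend and .01 elsewhere; TAU .03 | −.0091 | −.0009 |
| RIWP .04 and .01 likewise; TAU .025 | −.0009 | +.0009 |

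In the second row overall loss is about 19%: TAU 1 − .97⁴ = .115; RIWP, with about half the sites in each group, (1 − .85⁴ + 1 − .99⁴)/2 = .259; their mean is .187. Over 32 months −.0091 per year is −.0091 × 32/12 = −.024 SD. The third row loses about 10%, as the protocol plans, and shows no material bias.

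A hand example gives a similar order. Suppose one site's trend differs by .5 SD, it keeps 27/30 in RIWP but 18/30 in TAU, and every other site keeps 27/30 in both arms. The shift is .5 × (27/135 − 18/126) = .029 SD. Both the .5 SD and the 10% versus 40% loss are assumptions, and this is a completers' mean shift that ignores interim outcomes.

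**5. The sandwich provision.** In the same model without site terms and with no true effect, sandwich errors clustered on the five CBOs with a normal reference gave type I error of about .15 to .16. With a 5/4 correction and t on 4 df it was about .05. Sandwich errors clustered on persons gave .04 to .055.

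**The case against.** Four objections have force.

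- **The covariate vector is undefined.** The text excludes only a CBO random effect, and fixed site indicators in the covariate vector would be compatible with it. A covariate list is often left to the SAP, which is not shown. This stands in part: it cannot be claimed that site will certainly be absent. But the protocol nowhere names CBO as a covariate, its list of demographic, control and moderator variables omits CBO site, and the vector shows no products with Time. What the protocol does fix is a reason that points the wrong way.
- **Sandwich errors are planned.** The figures in step 2 describe an uncorrected model-based standard error, which is not the proposed analysis. This stands. A reader might infer that the Aim 1 test will be conservative or underpowered; the documents do not support that. Sandwich errors leave the estimate and the missing-data conditioning as they are, and the Aim 1 paragraph mentions no small-sample correction for five clusters.
- **The missing-data gap is partial.** A reader might infer that any dropout that varies by site breaks the missing-at-random assumption and biases B_03. It does not: with equal site-dependent dropout in both arms there was no bias. Interim outcomes carry some site information, race/ethnicity and birthplace would largely identify the African refugee site if used as covariates, and imputation is a fallback.
- **The model is provisional.** The protocol says that the longitudinal form will be chosen later from comparison-sample data. That sample has no CBO nesting, so it cannot settle whether site belongs in the Aim 1 model.

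**Conclusion.** The point holds as a modest improvement to the principal analysis. The stated reason for omitting a CBO random effect is reversed, no other CBO term is named for Aim 1, and Aim 2 treats the same participants differently. With balanced, complete data B_03 is unbiased and the power of .91 is confirmed. At an ICC of .03 the gain is about one power point, corresponding to a model-based standard error about 2 to 3% too large; this rests on alpha .05 two-sided and, for the slope model, on an assumed site variance in trend that the protocol does not give. Bias requires dropout that differs by site and arm and is tied to site trend. It was about .02 to .03 SD under severe assumed patterns and negligible at the planned 10% attrition. These figures give no ground for calling the Aim 1 test invalid or underpowered.

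**What to change.** In the Aim 1 equation, add four CBO indicators and their products with Time as fixed effects, and do the same in the matching secondary-outcome models. Include CBO in any imputation model. Replace the sentence that justifies the omission with one saying that CBO is included because randomization was stratified by it. If cluster-robust errors are kept, state the cluster level and, for clustering on five CBOs, a small-sample correction.

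Cost: a few lines of wording and eight parameters (4 + 4) against about 270 retained participants (300 × .9). No new data are needed, since site is known for everyone at randomization.

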**Secondary Aims.** (a)   Examine mechanisms of intervention effectiveness. This secondary aim will be examined through structural equation modeling (SEM) to provide tests of mediation effects through which outcomes are impacted by hypothesized mechanisms. The same models for changes in outcomes which are developed on the random sample^110^ will be used in these analyses. These analyses assess whether differences in outcomes between treatment groups are due to changes observed in protective factors from baseline to post-intervention.^111^ Significant indirect effects are anticipated linking the RIWP intervention with lower follow-up levels of distress, stressors, and economic precarity, via pre-to post-intervention increases in protective factors. Bootstrapped standard errors^105^ will be used to derive confidence intervals for these mediated effects; standard errors will be adjusted for clustering of participants within CBOs using sandwich estimators.^106^ (b) Explore whether race/ ethnicity, biological sex, gender identity, sexual orientation, age, and SES moderate intervention impact. For this secondary aim, stratification variables will be incorporated as level 2 covariates in the models described above. Moderation will be assessed via interactions between the multiple levels of treatment and each of these moderators.^107^ (c) Track local/state policy changes to obtain preliminary estimates of effects of these structural interventions on mental health, stressors, and economic precarity using propensity score matching. This aim will evaluate the impact of receiving the structural interventions which are the outcome of Aim 3 on mental health, stressors, and economic precarity. We propose to use propensity scores, but in this case where the treatment is receiving a structural intervention. Propensity scores will be developed using baseline data to predict the probability of receiving a structural intervention. We will then assess the impact of these interventions using matched samples in random effects models. Mediation will be examined using Sobel’s test to examine whether RIWP effectiveness had an indirect effect on mental health, stressors, and economic precarity through structural interventions (local/state policy changes).^108–110^ This is a secondary aim because, while important, there is not enough information to assess power a priori.

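### Aim 1 rests on a sandwich variance over only five CBOs with no small-sample method named, and the stated power of .91 does not fit a valid version of it; one-arm Learning Circle clustering also has no term

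*Protocol*

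**What the plan says.** Protocol, Data Analysis/Statistical Considerations, Aim 1: "we propose a linear model with random effects for individuals". Because randomization is within CBO, "there is not an explicit random effect for this included, but we do propose to use sandwich estimators", the purpose being "to adjust standard errors for any unexpected impacts of this clustering". The clustering unit is therefore the CBO, and Objectives/Aims gives five of them. The target is B_03, the difference in slopes between arms. The equation also carries a covariate vector whose members are not listed. The mediation analysis under Secondary Aims uses the same device: "standard errors will be adjusted for clustering of participants within CBOs using sandwich estimators".

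Data Collection Procedures, Random assignment, specifies "a computerized algorithm that stratifies randomization by CBO site". RIWP implementation gives 30 RIWP participants per site (150 in all) and group delivery: "Meeting in weekly Learning Circles, newcomers and their student partners learn from each other during cultural exchange time". The waitlist arm does not receive RIWP until Months 29-35.

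The Power paragraph assumes a baseline-to-posttest correlation of .68 and 10% attrition in the CBO sample, and states an Aim 1 power of .91 for an effect of .3. An ICC of .03 is stated only for Aims 2 and 3, and the one null simulation reported is for Aim 2.

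**The concern.** A cluster sandwich estimates the variance from the spread between clusters. With five clusters that leaves about 4 degrees of freedom, so the estimate is noisy and, uncorrected, biased downward. Default large-sample inference then rejects too often, and it does so even when CBO clustering is absent. The intended safeguard can damage the test it is meant to protect, and that test serves the study's principal objective.

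A second, separate matter is that participants are randomized individually but treated in groups in one arm only. Shared circle experience can correlate RIWP outcomes and widen the true sampling error of the treatment contrast. For Aim 2 the protocol uses this kind of one-arm structure, with CBO random effects set to zero in the un-nested comparison arm. Aim 1 has no counterpart for circles.

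**Working it through.** **Inputs.** From the protocol: 5 CBOs, 150 per arm, 1:1 within CBO, r = .68, 10% attrition (135 per arm analysed, 27 per arm per CBO), d = .30. Assumed because not stated: two-sided alpha of .05; circles nested within CBOs; 1 to 3 circles per site; circle ICC of .03.

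**1. Reproduce the stated power.** Residual variance = 1 - .68² = .5376. SE = sqrt(.5376 × 2/135) = .0892. Noncentrality = .30/.0892 = 3.36. Power = Φ(3.36 - 1.96) = .92 (.918 with t on 267 df). This agrees with the stated .91. The calculation contains no clustering and uses large df.

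**2. Type I error of a five-cluster sandwich.** With equal CBOs and 1:1 allocation in each, the effect estimate is the mean of five within-CBO differences. The uncorrected sandwich variance is 4/5 of the usual variance of that mean, so the statistic is sqrt(5/4) times a t on 4 df.

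- Uncorrected, normal critical value: 2P(t4 > 1.96 × sqrt(4/5)) = 2P(t4 > 1.753) = .154
- G/(G-1) corrected, normal critical value: 2P(t4 > 1.96) = .122
- Uncorrected, t on 4 df: 2P(t4 > 2.776 × sqrt(4/5)) = .068
- Corrected, t on 4 df: .050

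Null simulations of a pre/post ANCOVA (8,000 runs per setting) and a five-wave slope model (10,000 runs per setting) agree: .147-.162, .115-.129, .064-.075 and .047-.055 in the same order. With no circle effect the ANCOVA gave .153 and .121 in the first two rows. With a circle variance of .03 and one circle per site it gave .156 and .120. Circle clustering does not drive these figures.

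**3. Power of the valid version.** Corrected sandwich, t on 4 df, critical value 2.776, noncentrality 3.36: power = .71 (.73 simulated). With a normal critical value, simulated power is .90-.93, but at the inflated error rates of step 2.

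**4. Circle clustering, RIWP arm only.** The circle component is .03 × .5376 = .0161, either added to the residual variance or taken out of it. With J circles in total and the component added, SE² = .5376 × 2/135 + .0161/J. For one circle per site: .00796 + .0161/5 = .01119, so SE = .1058. If standard errors are model-based or robust at person level, they still use about .0892, so type I error is 2P(Z > 1.96 × .0892/SE). The partially nested model uses Satterthwaite df (9.7 for one circle per site and 26 for two, component taken out). Each cell shows added / taken out.

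| Circles per site | SE | Type I error, SE ignoring circles | Power, CBO sandwich with t on 4 df | Power, partially nested model |
|---|---|---|---|---|
| 1 | .1058 / .1052 | .098 / .096 | .57 / .58 | .72 / .73 |
| 2 | .0979 / .0973 | .074 / .072 | .64 / .64 | .84 / .84 |
| 3 | .0951 / .0944 | .066 / .064 | .66 / .67 | .87 / .87 |

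If .03 is instead read as a share of the total outcome variance, the ANCOVA simulation gives larger effects: type I error about .08 (three circles per site) to .13 (one), and power of .61 to .50 for the corrected sandwich with t on 4 df.

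**The case against.** The strongest reply is that the protocol states no normal reference, no df and no alpha, and that such details are commonly left to a statistical analysis plan, which is not at hand. A reader might infer that the principal test will in fact reject 12-16% of the time under the null. The document does not support that: the rate depends on a normal critical value it never states, and the corrected sandwich with t on 4 df gives 5%. This part of the objection stands. It does not dispose of the point, because choosing the valid reference moves power from .91 to about .71.

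Three other tempting readings also fail.

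- Learning Circles might be taken as a joint cause of the inflation. If circles nest within CBOs, a CBO-level sandwich already absorbs them.
- The .03 ICC used for Aims 2 and 3 might be thought wrongly left out of Aim 1. It is a CBO-level value taken from neighborhood literature, and a common CBO effect cancels when both arms are randomized within each CBO. It says nothing about circles.
- The model might be read as excluding CBO altogether. Only a CBO random effect is excluded; the covariate vector is not enumerated and could include CBO.

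It can also be said that the model is provisional, since the protocol promises model exploration and further power analyses. That exploration uses the random comparison sample, which has neither CBO nesting nor circles, so it cannot settle either issue.

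**Conclusion.** The concern holds in conditional form. The stated variance method and the stated power do not fit together. With five CBOs, either the sandwich is judged against a normal critical value and type I error is about 12-15%, or it is corrected with t on 4 df and power at d = .30 is about .71 rather than .91. This rests on an assumed two-sided .05 test, roughly equal CBO sizes, and the protocol's own correlation and attrition. It needs no circle ICC.

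The Learning Circle gap is separate and its size is not known. With person-level or model-based standard errors, a circle ICC of .03 implies a type I error of roughly 7-10% for three to one circles per site. The documents give no circle ICC, size or number, so this is a scenario and not an estimate. The few-cluster problem also applies to the sandwich adjustment in the mediation models.

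**What to change.** Replace the five-cluster sandwich in the Aim 1 and mediation models with fixed effects for CBO (four indicators), which matches the randomization strata. Record each RIWP participant's Learning Circle and, in Aim 1, fit a circle random effect in the RIWP arm only, with Kenward-Roger or Satterthwaite df. If the CBO sandwich is kept, specify CR2 with a t reference on about 4 df.

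Restate Aim 1 power for the method chosen:

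- CBO sandwich with t on 4 df: about .71 with no circle effect, and about .57-.66 at an assumed circle ICC of .03.
- Partially nested model: a range over assumed circle ICCs and circle counts, for example about .73-.84 at .03 with one to two circles per site.

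The cost is revised analysis wording, one extra recorded variable (circle ID), and a less favourable stated power. Neither the sample size nor the randomization has to change for the analysis to be valid.
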